Digital self-help interventions (e-health) or interventions delivered on smartphones (mobile- or m-health) may bridge the resulting gap, as they are scalable, affordable and a convenient, user-friendly, low-threshold, anonymous and immediate way of delivering interventions in daily life [12]. Digital self-help and m-health interventions have been shown to improve resilience, well-being and emotion regulation and decrease symptoms of distress, depression, and anxiety [13–17]. Nevertheless, the effects were often only small to moderate; many m-health interventions lack a theoretical basis and additional studies with general population samples are needed [13, 16]. Moreover, digital interventions often result in low engagement, high attrition, and substantial dropout [18, 19]. Thus, improving users’ acceptance of the digital intervention is highly relevant for ensuring long-term usage. Nevertheless, a study suggested that more than 70% of adolescents would use an e-health intervention and that 32% would prefer an e-health intervention over traditional face-to-face support [20].

Fostering resilience, self- and emotion regulation as well as social information processing can present meaningful transdiagnostic targets for e- or m-health interventions. Resilience, defined as the ability of a person to function successfully despite aversive experiences and to adapt to a difficult situation, is a key protective factor against the negative health consequences of ACE [21, 22] and may thwart the development of mental health problems [23]. Pronounced resilience protects against negative consequences, while the experience of ACE is generally associated with lower resilience [23, 24]. Thus, to minimize negative effects on health, it is essential to promote the resilience of people affected by ACE through appropriate interventions [24].

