#### Usage data and data from the FACE epidemiological study

Participants’ use of the FACE self-help app (logins, number of visits and time spent on modules/submodules pages) will be recorded as a measure of adherence. Furthermore, the data assessed in the FACE intervention study will be linked to the data assessed in the FACE epidemiological study, which included, among other variables, ACE and sociodemographic variables.

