### Statistical analyses

Analyses will be conducted according to the intention-to-treat paradigm. Additionally, we will conduct per-protocol analyses, including participants who complete baseline and post-intervention assessments and log into at least four modules defined as minimal therapeutic exposure. The significance level will be two-sided at *p* ≤ 0.05. To test the efficacy of the intervention in the intervention group compared to the control group, we will use linear mixed models. The differential effects of the SER and SSIP components will then be tested with interactions between the component and time. These analyses will model random slopes and intercepts for participants, test the fixed effects of the condition, as well as repeated assessments over time, using data from all participants. Linear mixed models have the advantage that they can account for missing values through maximum likelihood estimation [74]. Cohen’s d and f will be calculated as effect sizes. Furthermore, we will calculate Reliable Change Indexes [75].

Potential predictors and moderators of intervention outcome, such as gender or ACE severity will be analysed using multiple linear regressions. To analyse the mediation hypotheses and the longitudinal interplay of the variables, we will conduct path and structural equation analyses. Analyses will be conducted in SPSS, R and Mplus. There are no statistical stopping rules in this trial.

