#### Sample size calculations

*Main effects*: We expect a moderate effect size of *f* > 0.25 for the comparison of the intervention and the waiting list control group and a small effect of *f* > 0.10 for the differential effects between SER and SSIP. Based on previous studies on web-based self-help interventions, we expect a correlation between the pre- and post-measurement of *r* = 0.6. Power analyses were conducted using G*Power [76] with a power of 0.8, an alpha error of 0.05. With three measurements, a sample size of 24 is required to detect a within-between interaction between the active intervention and the waitlist control group. A sample size of 162 is required to detect a small effect between the two active conditions and the waitlist control group.

*Intensive longitudinal data analysis*: Furthermore, the study combines data from the EMA with survey data in a multi-level model to investigate mechanisms and moderators of changes in well-being and resilience in the participants over the course of the study. Structural equation models including mediation analyses require a minimum sample of 241 for detecting a moderate effect (four latent and 25 observed variables [77]). This sample size will also allow accurate estimates of the regression coefficients, variance components and standard errors for multilevel analyses of the EMA data [78]. Sample size required for intensive longitudinal analysis is still a subject of ongoing research and it depends largely on (a) the effect size, (b) the number of measurements, and (c) the proportion of measures answered each day. Consequently, we aim to randomize up to 250 participants.

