#### Handling of missing data and dropout

Dropout is defined as participants who withdraw actively from the intervention after randomisation. All the other participants will receive an e-mail invitation to complete the post- and follow-up-questionnaires in any case. All dropout cases are part of the intent-to-treat sample, as they have been randomised and are included in the analyses. We will analyse the extent of missing data, explore the missing data patterns, and determine the type of missing data (Missing Completely at Random, Missing at Random, Not Missing at Random). Depending on the analysis, missing values will be replaced using multiple imputations. Sensitivity analyses will explore the impact of the imputation of missing values.

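### The efficacy model handles missing outcomes without the recorded app use, so the effect is overstated if low users both answer t2 less often and benefit less

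*Protocol article*

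**What the plan says.** All places are in the protocol article.

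- **Statistical analyses.** Efficacy is tested with linear mixed models: random intercepts and slopes for participants, fixed effects of condition and of repeated assessment. On missing outcomes: "Linear mixed models have the advantage that they can account for missing values through maximum likelihood estimation". No app-use variable is named.
- **Usage data and data from the FACE epidemiological study.** Logins are logged, and "number of visits and time spent on modules/submodules pages) will be recorded as a measure of adherence". The only other role given to use is in the per-protocol set, which requires at least four modules.
- **Data collection and analysis.** The outcome questionnaires are built into the app.
- **Handling of missing data and dropout.** Missing-data patterns will be explored and the mechanism classified. Then: "Depending on the analysis, missing values will be replaced using multiple imputations". Sensitivity analyses of the imputation follow. The section does not say whether the efficacy test is one of the analyses to be imputed, or whether app use informs the imputation.
- **Background.** The authors expect trouble here: "digital interventions often result in low engagement, high attrition, and substantial dropout".

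**The concern.** Maximum likelihood in this model in effect predicts a missing t2 value from the participant's arm and observed outcomes. In the app arm, those who answer t2 may be mostly people who used the app. If silent participants used it little and gained less, the model credits them with too much. The estimate then drifts from the effect of being offered the app towards the effect in those who used it.

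Three features make a link between non-use and missing t2 plausible. The questionnaires sit in the app. The e-mail invitation to later questionnaires is promised to those who have not actively withdrawn from the intervention. The authors anticipate low engagement. What is at stake is the size of the effect on resilience and well-being, which is meant to inform large-scale deployment. A cause of missingness that the trial already measures can be conditioned on at little cost.

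**Working it through.** **The plan's own figures.** The article sets the test level ("The significance level will be two-sided at *p* ≤ 0.05") and the power inputs ("with a power of 0.8, an alpha error of 0.05"). On efficacy it says: "We expect a moderate effect size of *f* > 0.25 for the comparison of the intervention and the waiting list control group". The comparison of the components uses f = 0.10, and the assumed pre-post correlation is 0.6. For the within-between interaction with m = 3 measurements and k groups, λ = f²·N·m/(1−ρ), df1 = (k−1)(m−1) and df2 = (N−k)(m−1).

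- f = 0.25, k = 2, N = 24: λ = 0.0625·24·3/0.4 = 11.25, df 2 and 44, power 0.835. The formula first reaches 80% at 23, rounded to 24 for equal groups.
- f = 0.10, k = 3, N = 162: λ = 0.01·162·3/0.4 = 12.15, df 4 and 318, power 0.801.

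Both stated sample sizes reproduce, and this point does not touch them.

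**Inputs for the bias.** From the article: correlation 0.6, three waves (t0, t1, t2), 1:2 allocation. Assumed, because the article gives none: the true effect (0.30 SD; also 0.50 SD, from d = 2f with f = 0.25), the share of non-users, their benefit b relative to users, and t2 response by use. Half of the effect is present at t1.

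**Hand check.** Let p be the share of non-users and r_u, r_n the t2 response of users and non-users.

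- Effect in users: d_u = d / [(1−p) + p·b]
- Share of users among responders: w = (1−p)·r_u / [(1−p)·r_u + p·r_n]
- Effect among responders: d_u·[w + (1−w)·b]

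Example with d = 0.30, p = 0.4, b = 0 and response 90% v 40%: d_u = 0.30/0.6 = 0.50; w = 0.54/(0.54+0.16) = 0.771; responder effect 0.386. The likelihood model pulls this back only slightly, because t0 and t1 carry limited information on who stopped using the app.

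**Large-sample simulation.** Likelihood estimate with condition, time and outcomes only (unstructured covariance). The 0.30 rows assume 15% missing t2 on the waiting list, the 0.50 rows 10%.

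| True effect | Non-users | b | t2 response, users v non-users | Hand: responders | Likelihood estimate | Excess |
|---|---|---|---|---|---|---|
| 0.30 | 40% | 0 | 90% v 40% | 0.386 | 0.37 | about 23% |
| 0.30 | 40% | 0 | 90% v 60% | 0.346 | 0.34 | about 12% |
| 0.30 | 50% | 0 | 90% v 40% | 0.415 | 0.395-0.404 | 32-35% |
| 0.30 | 50% | 0.5 | 90% v 40% | 0.338 | 0.335 | about 12% |
| 0.50 | 20% | 0 | 90% v 60% | 0.536 | 0.52 | about 5% |
| 0.50 | 40% | 0 | 90% v 30% | 0.682 | 0.66 | about 32% |
| 0.50 | 40% | 0.5 | 90% v 60% | 0.529 | 0.52 | about 4% |
| 0.50 | 40% | 0.5 | 90% v 30% | 0.568 | 0.56 | about 11% |

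Simulation error is about 0.01, so excesses of a few per cent are approximate.

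**Where the bias vanishes or reverses.**
- Non-users gain as much as users: 0.49-0.51 against 0.50, and 0.301 against 0.30.
- Non-users answer as often as users: 0.49-0.51 against 0.50.
- No effect in anyone: 0.01.
- Non-users gain 1.5 times as much (30% non-users, 30% of them answering): 0.46 against 0.50, an understatement of about 8%.

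**With app use in the missing-data model.** The estimates return to about 0.30 and to 0.49-0.51.

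**Precision.** With 167 against 83 participants, the standard deviation of the estimate rises from about 0.131 to about 0.135 (0.135/0.131 = 1.03). In the first row the bias is 0.37 − 0.30 = 0.07, about half a standard error (0.07/0.131 = 0.53).

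**The case against.** The strongest reply is that the article states nothing false. A likelihood-based mixed model is valid under missing at random. The missing-data section adds exploration of patterns, imputation and sensitivity analyses, and a list of imputation variables normally belongs in the analysis plan, which is not shown. This stands in part: the absence of such a list is no fault, and app use may well be examined when patterns are explored. But the article does name the method for the efficacy test and its terms, and the planned imputation is left conditional on the analysis. Imputing from the same variables as the mixed model would largely repeat its assumption.

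Second, nothing in the documents links use to benefit or gives response by use. E-mail invitations, reminders and weekly support weaken the link between use and response. This stands, which is why the sizes are conditional. The largest ones need non-users to gain nothing and to answer rarely.

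Third, recovery of the true value is partly built in: the simulation makes use the cause of the problem and then conditions on it. Logged use may be an imperfect stand-in. This also stands.

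A reader might infer more than the documents support:
- *Lower response among non-users is enough to bias the result.* It is not; they must also gain less, given their earlier outcomes.
- *The bias always favours the app.* It reverses if people stop because they have improved.
- *The trial may find an effect where none exists.* If the app works in nobody, the bias is essentially nil.
- *The plan excludes app use from missing-data handling.* It is silent on this.

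**Conclusion.** The point holds in conditional form. As stated, missing outcomes in the efficacy model are handled given condition, time and observed outcomes only. If low users both answer t2 less often and benefit less, the intention-to-treat effect on resilience and well-being is overstated: by about 10-35% in most scenarios where non-users gain nothing (5% in the mildest), and by about 4-12% if they gain half as much. These sizes rest on assumed shares, response rates and benefit ratios and are not a forecast for this trial. This is a worthwhile, inexpensive improvement to a standard method rather than an error that invalidates the analysis.

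**What to change.** For resilience and well-being, state that the planned multiple imputation applies to the efficacy analysis. Impute separately by arm. Use all outcome waves in both arms and, in the app arm, recorded use such as the number of modules opened up to each wave. Limit imputation of t4 to the groups assessed at t4. Fit the planned mixed model to the imputed data by randomised group, and report it beside the likelihood-only mixed model so that readers see how far the two differ.

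The cost is a few lines of analysis-plan text and imputation code, with no new data. The downsides are a slightly larger standard error (about 3% in the check above) and reliance on accurate usage logs.

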#### Sample size calculations

*Main effects*: We expect a moderate effect size of *f* > 0.25 for the comparison of the intervention and the waiting list control group and a small effect of *f* > 0.10 for the differential effects between SER and SSIP. Based on previous studies on web-based self-help interventions, we expect a correlation between the pre- and post-measurement of *r* = 0.6. Power analyses were conducted using G*Power [76] with a power of 0.8, an alpha error of 0.05. With three measurements, a sample size of 24 is required to detect a within-between interaction between the active intervention and the waitlist control group. A sample size of 162 is required to detect a small effect between the two active conditions and the waitlist control group.

*Intensive longitudinal data analysis*: Furthermore, the study combines data from the EMA with survey data in a multi-level model to investigate mechanisms and moderators of changes in well-being and resilience in the participants over the course of the study. Structural equation models including mediation analyses require a minimum sample of 241 for detecting a moderate effect (four latent and 25 observed variables [77]). This sample size will also allow accurate estimates of the regression coefficients, variance components and standard errors for multilevel analyses of the EMA data [78]. Sample size required for intensive longitudinal analysis is still a subject of ongoing research and it depends largely on (a) the effect size, (b) the number of measurements, and (c) the proportion of measures answered each day. Consequently, we aim to randomize up to 250 participants.

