### Trial design

The study is conceptualized as a single-centre randomized controlled trial comparing an active intervention group against a waiting list control group (see Fig. 1). The intervention consists of two components (SER and SSIP) which are further compared in a crossover design to examine the differential effects of the components. The allocation ratio of the number of participants in the control group to the number of participants in the intervention group is 1:2. Randomisation is performed using a computer-generated allocation sequence.

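### The stated requirement of 24 participants for a moderate effect in fact corresponds to a group difference above 1 SD; the planned 250 is adequate, but the stated power figures need correcting

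*Protocol article*

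**What the plan says.** For the primary comparison the protocol article states: "We expect a moderate effect size of *f* > 0.25 for the comparison of the intervention and the waiting list control group". For the two components it assumes a small effect of f > "0.10 for the differential effects between SER and SSIP". The other inputs are also given: "we expect a correlation between the pre- and post-measurement of *r* = 0.6" and "Power analyses were conducted using G*Power [76] with a power of 0.8, an alpha error of 0.05", with three measurements. It concludes that "a sample size of 24 is required to detect a within-between interaction between the active intervention and the waitlist control group", and that 162 are needed for the small effect across the two active conditions and the waiting list. Under Trial design, "The allocation ratio of the number of participants in the control group to the number of participants in the intervention group is 1:2". The target of up to 250 follows from a minimum of 241 for the structural equation models and from the EMA analyses, not from the 24 or the 162.

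**The concern.** A total of 24 to detect a moderate difference between two groups is implausibly small. In a within-between interaction, f measures the spread of the group-by-time cell effects, and the correlation is applied separately. The familiar labels (0.10 small, 0.25 moderate) therefore do not carry over to a difference between groups at t2. If the labels do not match the inputs, readers are told that a moderate effect needs 24 people and that a small effect is covered by 162, and neither statement is right. The Background also says of digital interventions that "the effects were often only small to moderate", so the lower range of effects is the one for which readers will want a correct power statement.

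**Working it through.** **Inputs.** From Sample size calculations: f = 0.25 and f = 0.10, r = 0.6, m = 3 measurements, power 0.80, alpha 0.05. From Statistical analyses: "The significance level will be two-sided at *p* ≤ 0.05". From Trial design: control to intervention 1:2. Assumption: moderate means d = 0.5 and small means d = 0.2.

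**1. Reproducing the plan's figures.** G*Power default: noncentral F with lambda = f² × N × m / (1 − r), df1 = (k − 1)(m − 1), df2 = (N − k)(m − 1).
- k = 2, f = 0.25, N = 24: lambda = 0.0625 × 24 × 3 / 0.4 = 11.25, df 2 and 44, power 0.835. N = 22 gives 0.797. So 24 reproduces (next total with equal groups).
- k = 3, f = 0.10, N = 162: lambda = 0.01 × 162 × 3 / 0.4 = 12.15, df 4 and 318, power 0.801. N = 159 gives 0.793. So 162 reproduces.
- With f defined from partial eta-squared instead, f = 0.25 with k = 2 needs 80-82, so that definition was not used.

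**2. What f = 0.25 means there.** Let p be the share in the intervention group and c_j the group difference at visit j minus its mean over visits, in SD units. Then f = √[p(1 − p) × mean(c_j²)]. Let D be the difference at t2.
- Linear build-up (0, D/2, D): mean(c²) = D²/6.
- Full effect by t1 (0, D, D): mean(c²) = 2D²/9.

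| Allocation | Pattern | f per 1 SD | D at f = 0.25 | f at d = 0.5 |
|---|---|---|---|---|
| 1:1 | linear | 0.204 | 1.22 | 0.102 |
| 1:1 | full by t1 | 0.236 | 1.06 | 0.118 |
| 1:2 | linear | 0.192 | 1.30 | 0.096 |
| 1:2 | full by t1 | 0.222 | 1.13 | 0.111 |

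**3. Total needed for d = 0.5 at 1:2.**
- Interaction test: 141 (linear, power 0.802) or 108 (full by t1, power 0.810). At N = 24, power is 18% or 23%.
- Baseline-adjusted t2 comparison, residual variance 1 − 0.6² = 0.64: the normal approximation is 4.5 × 2.80² × 0.64 / 0.25 ≈ 90. By noncentral t, 90 gives 0.789 and 93 gives 0.803, so 93. At N = 24, power is 28%.

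**4. What f = 0.10 means in the three-group layout of the 162 (equal groups).**
- Both app arms alike: 0.10 / 0.192 = 0.52 SD (linear) or 0.10 / 0.222 = 0.45 SD (full by t1).
- Staggered, one arm (0, D, D), the other (0, 0, D), control flat: 0.10 / 0.272 = 0.37 SD.

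**5. What 250 delivers.** For d = 0.5 at 1:2 with complete data, power is 96.9% (interaction, linear), 99.4% (interaction, full by t1) and 99.6% (adjusted comparison). The detectable difference at 80% power is 2.80 × √[0.64 × (1/n1 + 1/n2)].

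| Comparison | Complete | 30% lost | 40% lost |
|---|---|---|---|
| App vs waiting list, t2 (83/167, 58/117, 50/100) | 0.30 | 0.36 | 0.39 |
| SER vs SSIP, t1 (83, 58, 50 per arm) | 0.35 | 0.42 | 0.45 |

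For 0.2 SD, app versus waiting list, power with complete data is 46% (adjusted) or 30-39% (interaction). The loss rates are assumed; the Discussion calls dropout high but gives no rate. An even split of the app group is also assumed.

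**The case against.** Three objections have weight. First, the arithmetic is right: both stated sizes reproduce, and the protocol states f, never d = 0.5. That stands. The fault lies in the label attached to the input, and d = 0.5 is a conventional reading. But no ordinary reading makes 1.1-1.3 SD moderate.

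Second, the 24 determines nothing. That also stands. A reader might infer that the trial is underpowered for its primary comparison, or that approval was sought on a misleading number. The documents support neither. The target comes from the structural equation and EMA analyses, 250 could lose (250 − 141)/250 ≈ 44% before reaching the largest corrected requirement, and no ethics submission is shown.

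Third, the planned analysis is a linear mixed model with random slopes and intercepts, not the adjusted comparison or the omnibus interaction used here. The totals are therefore approximations, which is why a range is given. Every route at 1:2 still gives nearly four times 24 or more (93/24 ≈ 3.9; 141/24 ≈ 5.9).

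The Background remark on small to moderate effects carries no number, so it cannot by itself show that the true effect lies below the one assumed.

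**Conclusion.** The concern holds as a fault in the stated figures, not in the size of the trial. The 24 is the requirement for a t2 difference of about 1.06-1.22 SD with equal groups (1.13-1.30 SD at 1:2), not for a moderate effect. It understates the need for d = 0.5 at 1:2 by a factor of about four to six. The 162 is tied to a difference of 0.37-0.52 SD, depending on the pattern of effects, not to a conventionally small one. At 250 the primary comparison is well powered for d = 0.5, but effects near 0.2 SD are not powered, for either the app or the component comparison. These conclusions rest on r = 0.6 between visits, equal variances, the patterns of effect shown, and d = 0.5 and d = 0.2 as the meanings of moderate and small.

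**What to change.** Withdraw 24 as the requirement for a moderate effect, and restate power as standardised differences with r = 0.6 and 1:2 allocation, in two separate statements:

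- **App versus waiting list at t2, baseline-adjusted:** 250 randomised detects about 0.30 SD with complete data, and about 0.36 or 0.39 SD if 30% or 40% are lost (marked as assumed rates). Power for 0.2 SD is at most about 46%.
- **SER versus SSIP at t1, baseline-adjusted, about 83 per app arm:** the detectable difference is about 0.35 SD with complete data and 0.42-0.45 SD at 30-40% loss, so a conventionally small differential effect is not powered. This statement should be kept because the component comparison is a stated secondary objective.

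If f is retained anywhere, state its definition and the group difference it stands for. The cost is a few restated sentences; recruitment, design and analysis are unchanged.

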### Secondary objectives

The secondary goals of this study are.

1) to test the efficacy of the FACE self-help app in improving self-efficacy for managing emotions and problem-solving as facets of self- and emotion regulation, fear of negative evaluation and social avoidance as facets of social skills and social information processing, as well as self-esteem (secondary outcomes).

2) to test the differential effects of the self- and emotion regulation (SER) and the social skills and social information processing (SSIP) components on all outcomes. We hypothesize that SER will specifically improve self-efficacy for managing emotions and problem-solving and thus will have a greater effect on these variables than will SSIP. Similarly, we expect that SSIP will specifically improve fear of negative evaluation and social avoidance and thus will have a greater effect on these variables than will SER.

3) We aim to analyse the effects of the FACE self-help app on real-life ecological momentary assessment data in affective states, distress in several areas of life, social interactions, the use of coping strategies and resilience. We expect that the FACE self-help app will improve these variables compared to the waiting list control group.

4) Finally, we assess the degree of satisfaction of the participants with the FACE self-help app.

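### The sample size of 162 is for a three-group interaction that includes the waiting list; for the SER-versus-SSIP difference it gives about 72% power, not 80%

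*Protocol article*

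**What the plan says.** All references are to the protocol article.

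- **Secondary objectives.** The second aim is "to test the differential effects of the self- and emotion regulation (SER) and the social skills and social information processing (SSIP) components on all outcomes". The hypotheses are directional between components: SER should do more than SSIP for managing emotions and problem-solving, and SSIP more than SER for fear of negative evaluation and social avoidance.
- **Statistical analyses.** Intervention against control is tested with linear mixed models. The component effects are then tested separately, as component-by-time interactions.
- **Sample size calculations.** Two effect sizes are set. The larger, f > 0.25, is for the app against the waiting list. The other is "a small effect of *f* > 0.10 for the differential effects between SER and SSIP". The pre-post correlation is taken as 0.6, and G*Power is run at 80% power and 5% alpha. For the larger effect the section gives 24 participants, measured three times. For the smaller one: "A sample size of 162 is required to detect a small effect between the two active conditions and the waitlist control group".
- **Trial design.** Control to intervention is 1:2, and the components are compared in a crossover.
- **Target.** Up to 250 are to be randomised. This follows from a requirement of 241 for the structural equation models, not from 162.

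**The concern.** The effect size of 0.10 is introduced "for the differential effects between SER and SSIP", but the number attached to it is for a comparison that also contains the waiting list. These are different tests. A three-group interaction has four numerator degrees of freedom, uses the whole sample, and responds to any difference among the three groups, including app against waiting list. The component hypothesis is a contrast between two arms that together hold two thirds of the sample.

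No other number is given for f = 0.10, so a reader will take 162 as the size at which the component aim has 80% power. If that is wrong, a null SER-SSIP result from a sample near 162 would be given more weight than it deserves, and the published justification for a secondary aim would not support it.

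**Working it through.** **Inputs from the protocol article:** f = 0.25 and f = 0.10, r = 0.6, alpha 0.05, power 0.80, three measurements, within-between interaction, allocation 1:2.

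**Assumptions added here:** sphericity (epsilon = 1), equal split of the active group between the two orders, f = 0.10 taken as the exact value, and loss treated as complete-case loss.

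**Formula (G*Power, repeated measures, within-between interaction).** With N participants, k groups, m measurements and correlation r:

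- noncentrality λ = N × f² × m / (1 − r)
- df1 = (k − 1)(m − 1); df2 = (N − k)(m − 1)
- power from the noncentral F distribution.

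**Step 1: identify the method.** For f = 0.25, k = 2, m = 3, the smallest N with equal groups is 24 (λ = 24 × 0.0625 × 3 / 0.4 = 11.25). This matches the plan.

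**Step 2: reproduce 162.** For f = 0.10, k = 3, m = 3:

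- λ = 162 × 0.01 × 3 / 0.4 = 12.15; df1 = 4; df2 = 159 × 2 = 318
- power = 0.801; at N = 161 it is 0.798.

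So 162 is exactly the three-group, three-measurement interaction, and the plan's sentence names those three groups. Two other settings come close: two groups with two measurements gives 160, and two groups with three measurements at r = 0.5 gives 164. Neither gives 162 or fits the stated inputs.

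**Step 3: the two-arm test at 162.** Active participants: 162 × 2/3 = 108. For k = 2, m = 3, f = 0.10:

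- λ = 108 × 0.075 = 8.10; df1 = 2; df2 = 106 × 2 = 212
- power = 0.717.

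**Step 4: number needed for 80%.**

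- λ = 130 × 0.075 = 9.75; df1 = 2; df2 = 256; power = 0.800
- 130 active × 3/2 = 195 in total, before dropout.

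**Step 5: power at the planned maximum.** 250 × 2/3 ≈ 167 active. The article gives no loss rate, so these rates are assumed.

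| Assumed loss | Active analysed | Power, SER vs SSIP, three measurements |
|---|---|---|
| 0% | 167 | 89% |
| 10% | 150 | 86% |
| 20% | 133 | 81% |
| 22% | 130 | 80% |
| 30% | 116 | 75% |
| 40% | 100 | 68% |

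**Step 6: first period only (t0 to t1), if the analysts chose to rely on it.** For m = 2, λ = N × 0.01 × 2 / 0.4 = 0.05N and df1 = 1. At 108 active, power is 63%. For 80%, 160 active are needed, or 160 × 3/2 = 240 in total. At 167 active, power is 82% with no loss.

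**The case against.** **The sentence says three groups, so it may be correct as written.** It is correct for the test it describes. But the paragraph sets f > 0.10 for SER against SSIP and offers no other number for it, so the mismatch remains.

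**162 does not set the size of the trial.** This stands. The target of up to 250 exceeds the corrected 195. A reader might infer that the component aim is underpowered even at 250 unless there is almost no dropout. The documents do not support that: with the planned three measurements, 80% survives about 22% loss. The mixed models also use partial data, and participants who have not actively withdrawn are still invited to later assessments, so complete-case loss is a cautious approximation. Against this, 250 is a ceiling, no loss rate is given, and the Discussion itself calls dropout in self-help interventions high.

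**The shortfall depends on the test and on what f means.** This stands in part. If all of f = 0.10 fell on a single one-degree-of-freedom crossover contrast over three measurements, 108 active participants would give 80.9%. If 0.10 were a three-group f due only to SER against SSIP, with the waiting list midway, the two-group f would be 0.10 × √1.5 = 0.122 and power 88.3%. The article states neither and did not compute 162 in either way.

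**Only the first period separates the arms.** A reader might infer this, since both arms have had both components by t2. But in the crossover the arms again receive different components between t1 and t2, in reverse order. The plan does not restrict the comparison to t0-t1. Carry-over could be a reason to do so, but the article does not choose that.

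**A significant three-group test could be mistaken for a component difference.** Such a test could indeed be significant with identical components. Nothing in the article says it will decide the component hypothesis, though, and the analysis section tests component effects separately. How often this would happen cannot be calculated without effect sizes that the article does not give.

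**Conclusion.** The point holds as a fault in the stated justification of a secondary aim. The figure of 162 is the size for a three-group by three-time interaction including the waiting list. For the SER-versus-SSIP interaction to which f > 0.10 is assigned, it gives about 72% power, some 8 percentage points below the stated 80%. The matching requirement is 130 active participants, 195 in total, which is 33 more than stated (195 − 162).

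This rests on the plan's own f, r, number of measurements and method, plus equal active arms and sphericity. It does not show that the trial as planned is too small, and no primary inference is affected.

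**What to change.** In Sample size calculations, replace the sentence giving 162 with the two-arm calculation: for f = 0.10, r = 0.6 and three measurements, 130 analysable participants in the two active arms, 195 in total at 1:2, before dropout.

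Add the power for this contrast at up to 250 randomised (about 167 active): 89% with no loss, 81% at an assumed 20% loss and 75% at an assumed 30% loss, or the equivalent at the loss the team expects.

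State in Statistical analyses that the component hypothesis is judged by the SER-SSIP contrast and not by the three-group test. If the team intends to rely on the first period only, for example because of carry-over, say so and give about 160 active (240 in total) instead.

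The cost is wording and a less favourable stated figure for a secondary aim. No extra participants are needed, and the planned three-measurement analysis stays as it is unless the team chooses the first-period comparison.
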